### 2.6. Data Analysis

The analyses will be carried out with the statistical package IBM SPSS Statistics version 22.0 for Windows [78]. First, the sociodemographic characteristics of the sample will be analyzed with descriptive statistics, calculating the mean and standard deviation of the scores in the different questionnaires administered. Next, a missing-value analysis and the Little Missing Completely At Random (MCAR) test will be performed to determine whether or not the distribution of missing values is random, and therefore whether the last observation made (LOCF) can be used. Internal consistency will be explored using Cronbach’s alpha.

As the sample size is expected to be less than 50, the normal distribution of the variables will be verified with the Shapiro–Wilk normality test. Depending on the result of this test, parametric or non-parametric repeated measures analysis will be carried out to verify whether or not the differences in the scores of the variables measured at different times are statistically significant. In case the variables follow a normal distribution, parametric repeated measures analysis will be carried out, specifically the Multivariate Analysis of Variance (ANOVA), and in case the variables do not follow a normal distribution, non-parametric repeated measures analysis will be carried out, specifically the Friedman test. If the repeated measures analysis show statistically significant differences between the evaluation time points, post-hoc comparisons will be carried out to correct the level of significance to avoid increasing the type I error. Thus, regarding adjustment for multiple comparisons, the Bonferroni correction will be carried out in case of having performed parametric analysis, and the Wilcoxon signed rank test in case of having performed non-parametric analysis in the comparison of means. More detailed information on this has been added in the data analysis section, explaining step by step which statistical analyzes will be carried out.

Finally, the Reliable Change Index (RCI), which assesses the clinically significant change obtained to determine in which variables the scores have approached those of the normative sample, will be calculated. A clinically significant change will be considered if the RCI score obtained is equal to or greater than 1.96 [79].

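### A normality pre-test chooses between two analyses with different targets and different error control, and the non-parametric one has no multiplicity correction for its pairwise tests

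*Protocol article*

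**What the plan says.** Section 2.6 sets out the group analysis as a sequence.

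- Missing values are examined first. Little's test decides "whether the last observation made (LOCF) can be used".
- Then "the normal distribution of the variables will be verified with the Shapiro–Wilk normality test". The reason given for this choice of test is "As the sample size is expected to be less than 50".
- The result selects the analysis: "Depending on the result of this test, parametric or non-parametric repeated measures analysis will be carried out". If normality is accepted, the analysis is a repeated-measures multivariate ANOVA. If not, "non-parametric repeated measures analysis will be carried out, specifically the Friedman test".
- Pairwise comparisons follow only a significant omnibus result, and their stated purpose is to keep the type I error from rising. For this purpose "the Bonferroni correction will be carried out in case of having performed parametric analysis", and on the other route "the Wilcoxon signed rank test in case of having performed non-parametric analysis in the comparison of means".

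Table 4 repeats, for the group results, that the data will decide which family of tests is used. Section 2.6 does not say whether normality is judged per variable, per time point or for all variables together. A sentence there points to the data analysis section for more detail, but it stands in that section, and what follows does not settle the matter.

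**The concern.** Two things are wrong with the rule as written.

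First, a preliminary test on the data decides what is estimated. Repeated-measures ANOVA compares means. The Friedman test compares ranks within each participant. The Wilcoxon signed rank test works on ranked differences, although the text calls it a comparison of means. The check is also aimed at the variables, whereas a repeated-measures analysis depends on the behaviour of residuals or within-person differences.

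Second, the routes do not control error in the same way. Wilcoxon is placed where a correction belongs, so read literally the non-parametric pairs are each tested at the unadjusted level. Hypothesis 2 concerns maintenance of gains for two years. False differences among post-treatment and follow-up visits would look like relapse or further improvement, which is the question that hypothesis asks.

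**Working it through.** **Inputs**

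- Sample: 60 participants and 35% loss (section 2.1). 60 × (1 − 0.35) = 39, which agrees with the expectation in section 2.6 of fewer than 50.
- Time points for the questionnaires: quarterly follow-up for 24 months gives 24/3 = 8. With pre- and post-treatment that makes 10 (section 2.2, Table 3). Three time points is used as a smaller case.
- Pairs: 10 × 9/2 = 45, and 3 × 2/2 = 3.
- Assumed because not stated: two-sided alpha 0.05 for the group tests, 0.05 for Shapiro–Wilk, within-person correlation 0.5, all pairs compared.

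**1. How often a truly normal score is sent to the non-parametric route**

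With k independent tests and a switch on any rejection, the chance is 1 − 0.95^k.

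| Tests | Formula | Simulated, n = 39 |
|---|---|---|
| 1 | 5% | – |
| 3 | 14.3% | 14.2% |
| 10 | 40.1% | 36–42% (correlations 0 to 0.7) |

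For moderately skewed scores (lognormal, assumed) the non-parametric route was chosen in 99–100% of runs.

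**2. Pairwise thresholds**

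Bonferroni gives 0.05/45 = 0.0011 with 10 time points and 0.05/3 = 0.0167 with 3. Unadjusted Wilcoxon uses 0.05.

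**3. Nothing changes at any time point (normal scores)**

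Chance of at least one false pairwise finding:

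| Time points | Bonferroni paired t | Wilcoxon, unadjusted, no omnibus gate | Wilcoxon, unadjusted, after significant Friedman |
|---|---|---|---|
| 3 | 4.8% | 13.1% | 4.6% |
| 10 | 4.0% | 65.5% | 4.6% |

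The whole two-stage rule, with normal or skewed scores, gave 3.3–4.8%. Under this null the omnibus gate does its job.

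**4. Scores improve after treatment and then stay level**

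This is the pattern that hypotheses 1 and 2 predict. It was simulated with a pre-treatment shift of one standard deviation and all later visits equal. The pairs with no true difference number 9 × 8/2 = 36 with 10 time points, and 1 with 3 time points. Friedman is now significant because of the real change, so it no longer protects those pairs.

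| Time points | Bonferroni paired t | Wilcoxon, unadjusted, after Friedman | Wilcoxon with Bonferroni, after Friedman |
|---|---|---|---|
| 3 | 2.1% | 4.9% | 1.7% |
| 10 | 2.6% | 57.4% | 1.9% |

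A separate simulation of the 10-point case gave about 61% unadjusted and about 3.5% with Bonferroni. Both are plausible against simple bounds. One null pair tested at 0.05 errs about 5% of the time. Thirty-six independent tests would err 1 − 0.95^36 = 84% of the time, and positive dependence between the pairs lowers that.

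**The case against.** The strongest defence has four parts.

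- **The gate.** Pairwise tests run only after a significant omnibus test, and under the global null that holds the error near 5%. This stands. A reader might infer that the two-stage rule inflates type I error in general, and the calculation does not support that.
- **Intent and extent.** The text says that the post-hoc step exists to protect the type I error, so the Wilcoxon clause may be loose wording. Nor does it say that all 45 pairs will be compared. With 3 time points the gap is small (4.9% against 2.1%). This stands as a limit on the size, but the sentence still names no correction.
- **Chance against real skew.** A reader might infer that chance rejections mostly decide the route. The 40% figure needs a test at each of ten time points and a switch on any failure. With one test it is 5%. Skewed scales would switch because of their real shape. That makes the uncorrected route more likely to be used, so the multiplicity gap matters more.
- **Reach.** The Reliable Change Index, with its fixed 1.96 cut-off, the visual analysis, attendance and satisfaction do not depend on the normality test, and the study is a pilot. This stands, and it confines the point to the group comparisons.

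Two further readings are tempting and fail. One is that the routes treat missing data differently. The LOCF step comes before both and is tied to neither, and both omnibus tests as named need complete rows. The other is that only the rank-based route lacks effect sizes or intervals. Section 2.6 states none for either route.

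**Conclusion.** The point holds for the group comparisons, on two grounds. A normality test on the data selects between analyses of means and of ranks, and only the parametric route has a genuine multiplicity correction. Under the course that the trial expects, the uncorrected route gives at least one false pairwise finding in about 5–6% of trials with 3 time points and about 57–61% with 10, against about 2–4% with Bonferroni. A truly normal score would take that route by chance in 5% of cases (one test), about 14% (3 time points) or about 40% (10 time points). The error rates rest on n = 39, correlation 0.5, two-sided alpha 0.05 and testing of all pairs. The size depends mainly on how many time points are compared.

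**What to change.** At minimum, state that the Wilcoxon pairs receive the same Bonferroni or Holm adjustment as the parametric pairs. This is one added clause. In the 10-point case above, Bonferroni brings the error from 57.4% to 1.9%. The cost is somewhat lower power for each pairwise test.

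Preferably, remove the normality gate and name one repeated-measures analysis for every continuous outcome. One example is a mixed model with time as a categorical factor, which the planned software offers as SPSS MIXED. State the adjustment for pairwise contrasts, check residuals, and give a rank-based or bootstrap analysis as a sensitivity check. The cost is wording, plus reliance on a model for skewed scales, which the sensitivity analysis is there to test. Table 4 should be brought into line.

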The multiple baseline design involves the application of the treatment variable in a staggered way over time, through different observational units. This design is suitable for health services research interventions that are focused on changing patient behavior. This methodology facilitates a systematic comparison of pre-intervention and post-intervention measures [35], and conducting a preliminary assessment of a novel intervention [36]. Like randomized controlled trials (RCTs), the multiple baseline design can demonstrate that a significant change in behaviour has occurred and that is result of the intervention. One of the main limitations is that each participant must show changes only when the intervention is applied, and this issue, at a practical level is complicated, can make it difficult for the researcher to draw clear conclusions about the impact of the intervention. In order to reduce this limitation and improve the internal validity, researchers start treatment at different times across settings, behaviors, or people [37]. The multiple baseline design has advantages over the RCTs because this design requires fewer population groups and communities and they may act as their own controls [35]. In this sense, researchers often use this design with several people at once addressing the issue of external validity [37].

In the present investigation, all consecutive patients who are selected to undergo BS and who present anxiety or depressive symptoms or at least one diagnosis of ED, will be asked to participate. Once inclusion criteria are met (see “Inclusion and exclusion criteria” section), each patient will be randomly assigned to one of the multiple baseline conditions: 8, 12, or 15 evaluation days before the intervention. These multiple baseline conditions have been chosen following the current guides for single-case designs [34,38].

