### 2.1. Sample and Recruitment

The study recruitment will start in September 2020 until December 2024. The study will be conducted in a public mental health center in Spain (Mental Health Unit of the Regional Hospital of Vinaròs, Castellón). Participants will be people over 18 years of age who have anxious or depressive symptoms, or at least one diagnosis of EDs according to Diagnostic and Statistical Manual of Mental Disorders five edition criteria [39] and who have been selected for a subsequent BS.

To calculate the sample size, we drew on a study that proposed stepwise rules of thumb for pilot studies based on the target effect size and the size of the future trial [40]. Previous works that study the efficacy of CBT procedures either in person or online have shown large variations in effect sizes, obtaining mainly medium to large effect sizes [41,42]. Taking these data into account, and expecting a 90% powered main trial and assuming a sample loss of 35% [43] we established a sample size of 20 participants per experimental condition for the present study, that is, a total sample of 60 participants.

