The baseline and psychological intervention will be conducted between the period of acceptance for BS and the BS implementation, that last approximately one year in public health settings. The intervention will be carried out in an online group format through the Cisco Webex platform. The UP will be applied in twelve weekly 2-h online group sessions. To comply with the experimental design of the multiple baseline, when each participant completes the baseline evaluation, they will receive the first online session in individual format (to receive the first session in stages), then they will continue with the second session and the rest of the treatment in group format. The content of each session is shown in Table 2. Participants will receive the therapy support manual [11]. The online group will consist of five to eight participants, one therapist ([name]), and one co-therapist ([name]). For ethical reasons, if any of the patients feel uncomfortable during the study with the online group format, they may leave the group and receive individual onsite attention (treatment as usual). In this case, the content and estimated number of sessions will be the same, although the frequency will be stipulated by the mental health unit depending on its possibilities.

The study plans to conduct a follow-up assessment every three months until two years after treatment completion. All follow-ups will be conducted online. Considering the time interval of the baseline, the psychological intervention and the BS procedure, the two first follow-ups (three and six months after intervention) will be conducted before BS, and the rest will be conducted after BS. In addition, at the baseline and during treatment, the participants must fill out an online survey made up of 14 questions that will ask about the intensity of the emotions of happiness, sadness, anxiety, other emotions, difficulties in emotion regulation, body image, and emotional eating. Through this weekly evaluation, we expect to observe how the participants evolve in the different variables throughout the different treatment modules.

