Another aspect that we consider important to analyze is how the participants change their scores in each of the variables evaluated based on the content addressed each module. For this purpose, a visual analysis of the changes in the scores will be carried out, to see how the slopes change in the different phases of the study (evaluation and treatment), and in the different modules within the treatment. This visual analysis has been used in previous studies [21]. To carry out this visual analysis, the data from 19 questions that the participants will fill in weekly will be used.

Attendance at sessions will also be recorded to calculate the attendance rate, which will be used as an indicator of viability and acceptance of treatment by users. For the same purpose, quantitative and qualitative analyses will be carried out. At the quantitative level, the participants’ evaluation of and satisfaction with the treatment received will be evaluated using an ad hoc designed questionnaire (see “Measures” section). Qualitatively, participants will be asked to answer six main questions about treatment, and their answers will be analyzed by selecting and classifying the information through a segmentation process, identifying key themes and categories of analysis [80].

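### The tests named in section 2.6 use time only; the randomised 8/12/15-day start enters none of them, so the tested results are uncontrolled before-after comparisons

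*Protocol article*

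**What the plan says.** Section 2 (Materials and Methods) sets out a multiple baseline design in which "each patient will be randomly assigned to one of the multiple baseline conditions: 8, 12, or 15 evaluation days before the intervention". It gives the stagger and the random assignment as defences against selection, maturation and history, and says of the design in general that "the multiple baseline design can demonstrate that a significant change in behaviour has occurred and that is result of the intervention". Section 2.2 delivers session 1 individually at the end of each participant's baseline so that starts are staggered. It then moves to group sessions: "The online group will consist of five to eight participants".

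Section 2.6 names the analyses. At group level, "parametric or non-parametric repeated measures analysis will be carried out to verify whether or not the differences in the scores" measured at different times are significant: repeated-measures ANOVA if normality holds, Friedman if not, followed by Bonferroni or Wilcoxon comparisons. At individual level, an RCI of at least 1.96 marks change. For the repeated battery, "a visual analysis of the changes in the scores will be carried out, to see how the slopes change in the different phases" and modules. Table 4 repeats the group comparison over time points and the RCI as the expected results.

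The sample size statement in section 2.1 reads "assuming a sample loss of 35% [43] we established a sample size of 20 participants per experimental condition", 60 in all, and section 2.6 expects fewer than 50 participants for analysis.

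**The concern.** The feature that could separate treatment from the passage of time is the randomised start day. A test whose only factor is time does not use it. Whatever moves scores between assessments counts towards a significant result:

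- **Natural recovery or drift** over baseline and twelve weekly sessions.
- **Regression to the mean**, since entry can rest on moderate scores on the BDI-II or BAI, which are also primary outcomes.
- **Surgery**, since section 2.2 places the three- and six-month follow-ups before the operation and the rest after it.

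A second, separate matter is precision. Sessions 2 to 12 are delivered in therapy groups, and the named tests treat participants as independent. If members of a group change together, the standard errors are too small. This says nothing about causation, because the therapy groups are not the randomised factor.

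**Working it through.** **1. Is the randomised factor in any test?**

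| Analysis in section 2.6 | Data | Uses baseline condition? | Inferential? |
|---|---|---|---|
| Repeated-measures ANOVA or Friedman | Scores over time points | No | Yes |
| Bonferroni or Wilcoxon post-hocs | Pairs of time points | No | Yes |
| RCI of at least 1.96 | Each participant's scores | No | Yes, per participant |
| Visual analysis of slopes | 19-question battery | Uses phases; names no comparison of the three tiers | No |

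**2. Expected number analysed.** 60 × (1 − 0.35) = 39 in total and 20 × 0.65 = 13 per condition. This agrees with the statement that fewer than 50 are expected. The rule-of-thumb step behind the 20 per condition cannot be reproduced from the document, and nothing here depends on it.

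**3. What a time-only test does with drift.** Assumptions: two-sided 5%, one paired t-test, no treatment effect, and a drift of δ SDs of the change score. The non-centrality is δ√n. For δ = 0.30, 0.30 × √39 = 1.87 against a critical value of 2.02 on 38 degrees of freedom.

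| Assumed drift (SD of change) | Unadjusted | Bonferroni, 3 comparisons | Bonferroni, 45 comparisons |
|---|---|---|---|
| 0.20 | 23% | 12% | 2% |
| 0.30 | 45% | 28% | 6.5% |
| 0.50 | 86% | 73% | 36% |

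The 45 comparisons are all pairs of ten time points (pre, post and eight quarterly follow-ups): 10 × 9 / 2 = 45. The document gives no drift size, so the rows show a range and not an estimate.

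**4. Therapy groups.** The design effect is DE = 1 + (m − 1) × ICC, the actual type I error is 2 × [1 − Φ(1.96/√DE)], and the effective sample size is 39/DE. Groups start with 5 to 8 members. At 65% retention that is 5 × 0.65 = 3.25 to 8 × 0.65 = 5.2 completers. The ICC is assumed to be 0.02 to 0.10.

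- Low end: DE = 1 + 2.25 × 0.02 = 1.045; type I error 5.5%; effective n = 37.
- High end: DE = 1 + 4.2 × 0.10 = 1.42; type I error 10.0%; effective n = 27.

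**5. What the stagger can deliver.** It spans at most 15 − 8 = 7 days, and only the individual session 1 is assured before group sessions begin. Table 3 shows no BDI-II, BAI or MINI in the baseline phase, so the tiers can inform only the repeated battery and, in principle, BMI. As a rough guide, take a contrast of the 8-day and 15-day tiers near day 15 with an assumed standardised difference of 0.5, adjusted for an earlier measurement correlated 0.5 (residual SD √(1 − 0.25) = 0.87). Power is then about 31% with 13 per tier and 45% with 20 per tier.

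**The case against.** Five points can be made for the plan.

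- **The phase data are used.** A reader might infer that the plan throws away its causal evidence. It does not: the visual analysis compares slopes between evaluation and treatment. What is missing is any inference from that comparison and any stated comparison of the tiers.
- **The causal sentence is general and hedged.** It describes multiple baseline designs as a class. The same section warns that clear conclusions about impact may be hard to draw, and the Discussion asks for caution and further randomised trials. So the documents do not support a claim that the investigators will credit every change to the UP. That caution, however, rests on pilot status and does not say that the named tests are uncontrolled. The pre-treatment assessment placed before baseline is also a stated measure against testing effects.
- **Detail may sit in an analysis plan.** A group random effect might. The main point does not depend on that, because section 2.6 and Table 4 name the tests, and those tests do not match the role given to the stagger.
- **The drift percentages are for one unadjusted test.** This stands. Bonferroni on the parametric branch lowers them, by a lot if all time points are compared.
- **The randomised evidence is thin.** This also stands: a seven-day stagger, single items, sampling that changes from daily to weekly as treatment starts, and no main symptom scale at baseline. It limits what a tier-based test can show and makes plain labelling of the questionnaire results more important.

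**Conclusion.** The concern holds in a bounded form. The inferential tests that the article fixes use time only, the randomised 8/12/15-day start enters none of them, and the phase comparison is by eye. The tested before-after results therefore cannot separate the UP from drift, regression to the mean or, from nine months on, surgery.

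The sizes are illustrative. With 39 completers and an assumed drift of 0.30 SD of change, a single unadjusted paired test rejects in about 45% of trials with no treatment effect, and less often after Bonferroni. Ignoring therapy groups is a lesser, standard-error problem: a design effect of about 1.05 to 1.42 and a nominal 5% test running at about 5.5% to 10%, for assumed ICCs of 0.02 to 0.10 and about 3 to 5 completers per group. Neither the drift nor the ICC comes from the documents.

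It would be wrong to infer that a tier-based analysis would make the BDI-II, BAI or MINI results controlled, since these are not measured in the baseline phase. Feasibility results (attendance, satisfaction) are untouched. The change should be made, but the study does not stand or fall on it.

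**What to change.** 1. **Use the randomised tiers on the battery.** Keep the visual analysis and add a randomisation test that re-draws the 8/12/15 assignments, on a few items named in advance (for example sadness and anxiety). Support it with a multilevel phase model using actual time in days, with change at each participant's randomised start and participant random effects. The residual structure must allow for unequal spacing; an ordinary first-order autoregressive structure assumes equal spacing and does not suit daily then weekly data.
2. **Label the questionnaire results.** Describe pre-post and follow-up results on the BDI-II, BAI, MINI and secondary scales as uncontrolled, and say that follow-ups from nine months on also include the effect of surgery.
3. **Allow for therapy group.** Where a parametric model is used for the questionnaires, make it a mixed model with a therapy-group random effect. The Friedman branch cannot take one, so the plan should acknowledge clustering there as a limitation.

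Cost: analyst time, somewhat wider intervals, and a tier-based test that may well be inconclusive because its power is limited. The battery, start dates and group membership arise from the study as planned, so no new data collection or change to care is needed.

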The specific objectives pursued are: to evaluate adherence to treatment and clinical improvement in the primary and secondary measures after applying the UP and to study its long term clinical usefulness until two years after the intervention. Thus, the main hypotheses proposed for this study are: (1) statistically significant differences (reliable change index; RCI) will be obtained between the scores obtained at the pre-treatment, baseline, and post-treatment on the primary and secondary measures; (2) the improvements obtained after the application of the UP will be maintained in the long term (follow-ups of up to two years); (3) participants in the pilot study will report high adherence rates and high satisfaction scores regarding the treatment delivery format and its components.

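### The group-level pre-to-post change is reached only through an omnibus test and a Bonferroni post-hoc family that is not tied to the hypotheses

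*Protocol article*

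**What the plan says.** Section 2.6 sets a sequence for the group analysis. A repeated-measures test over the measurement times comes first (parametric, or Friedman if normality fails). Then: "If the repeated measures analysis show statistically significant differences between the evaluation time points, post-hoc comparisons will be carried out". On adjustment, "the Bonferroni correction will be carried out in case of having performed parametric analysis". The section does not list the occasions that enter the model or the comparisons that form the Bonferroni family, and it singles out no contrast.

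The hypotheses at the end of the Introduction are more specific. Hypothesis 1 concerns pre-treatment, baseline and post-treatment scores. Hypothesis 2 is that "the improvements obtained after the application of the UP will be maintained in the long term (follow-ups of up to two years"). Table 4, under individual results, also names comparisons of pre-treatment and of post-treatment with the follow-ups. Under group results it speaks only of comparing scores across time points.

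Table 3 schedules BDI-II and BAI at pre-treatment, post-treatment and the follow-ups, not in the baseline phase. Section 2.2 makes follow-up quarterly for two years and puts the first two follow-ups before surgery and the rest after it.

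On size, section 2.1 states: "we established a sample size of 20 participants per experimental condition for the present study, that is, a total sample of 60 participants", "assuming a sample loss of 35" per cent. Section 2.6 adds: "As the sample size is expected to be less than 50".

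**The concern.** The omnibus null is that the mean is the same at every occasion. The hypotheses ask something narrower: did scores change from before to after treatment, and did the change last? For BDI-II and BAI, which are not given during the baseline phase, hypothesis 1 reduces at group level to pre versus post.

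Two things follow if all scheduled occasions enter one model. The pre-post comparison shares its error rate with many pairs that nobody has asked about, so a real medium-sized improvement could be reported as non-significant. And the gate can be opened by change at the later visits, most of which follow bariatric surgery, so a significant omnibus result would say nothing specific about the psychological intervention. This matters most for BMI, which is also a primary outcome.

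Hypothesis 2 is affected in the opposite direction: a very strict threshold makes a true relapse harder to detect, which favours a conclusion that the benefit was maintained.

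**Working it through.** **Inputs from the article**
- Planned n = 60; loss 35%; completers 60 × 0.65 = 39, which agrees with the expectation of fewer than 50.
- Occasions for BDI-II and BAI: pre + post + 8 quarterly follow-ups = 10.
- Effect size: described as "obtaining mainly medium to large effect sizes", with no number.
- Power: "expecting a 90% powered main trial" refers to a future trial. No power is given for any contrast in this study, so there is no planned figure to reproduce.

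**Assumptions**
- Alpha 0.05 two-sided (not stated).
- Standardised paired change dz (mean change divided by the SD of the change) of 0.5 as the central case, with a range of 0.3 to 0.8.
- All 10 occasions enter one model, and the post-hoc family is all pairs.

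**Family size**
- All pairs: 10 × 9 / 2 = 45; alpha per pair 0.05/45 = 0.0011.
- Follow-up versus follow-up: 8 × 7 / 2 = 28.
- Pairs that the article names: 1 (pre-post) + 8 (post versus follow-up) + 8 (pre versus follow-up) = 17; 17 + 28 = 45.

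**Power for pre versus post**

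Paired t-test, noncentral t with 38 degrees of freedom and noncentrality dz × √39. At dz = 0.5 this is 0.5 × 6.245 = 3.12.

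| Family size | Alpha per test | Power at dz 0.5, n = 39 |
|---|---|---|
| 1 | 0.05 | 86% |
| 3 (three occasions only) | 0.0167 | 73% |
| 9 (pre-post and 8 post versus follow-up) | 0.0056 | 58% |
| 17 (all named comparisons) | 0.0029 | 49% |
| 45 (all pairs) | 0.0011 | 36% |

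One contrast against 45 pairs at other effect sizes, n = 39:
- dz 0.3: 45% against 6.5%
- dz 0.4: 68% against 17.5%
- dz 0.6: 95.5% against 59%
- dz 0.7: 99% against 79%
- dz 0.8: 99.8% against 92%

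The largest loss is 52 points, at dz about 0.445 (77% to 25%). With all 60 retained and dz 0.5, power is 97% against 67%.

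**The gate**
- Simulation at n = 39, 10 occasions, equal correlation of 0.5 (assumed), change kept at all follow-ups, dz 0.5. The multivariate omnibus test is significant in 72% of runs. Pre-post at 0.05/45 is significant in 37% ungated and 35% gated. The gate itself costs almost nothing; the correction does the damage.
- Same settings, but no pre-post change and a 0.5-SD shift at the six post-surgery visits: the omnibus test rejects in over 99% of runs.

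**Relapse under hypothesis 2**

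A 0.5-SD relapse at one follow-up, correlation 0.5 (so dz = 0.5), n = 39, is missed in:
- 64% of cases at 0.05/45;
- 41% at 0.05/8 = 0.00625, the first Holm step over eight contrasts;
- about 50% at 0.05/16 = 0.0031, the first Holm step over sixteen;
- 14% only at an unadjusted 0.05.

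**The case against.** The strongest reply is that the text never says all pairs. It leaves open both the occasions and the family, and a condensed article may leave these to an analysis plan that is not shown. That stands: a reader might infer that the plan fixes 45 comparisons, but this is the natural reading of post-hoc tests after an omnibus test over time points, not a statement. If only three occasions entered, the loss at dz 0.5 would be 13 points (86% to 73%). What the article does fix is the gate and the correction, with no contrast exempted.

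Second, both hypotheses are also assessed person by person through the Reliable Change Index with its 1.96 criterion, which neither the gate nor Bonferroni touches. That stands too, so it would be wrong to say that the trial's question can be answered only through the corrected comparison. But Table 4 lists the group tests as a separate result in support of clinical usefulness, and those are affected.

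Third, this is a pilot sized by a rule of thumb, and omnibus testing followed by Bonferroni is conventional and controls type I error. Both points are fair. They make this an improvement to the analysis rather than an error in it.

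Fourth, a loss of 50 points depends on its comparator. It holds near dz 0.45 to 0.5 against one unadjusted test. Against all 17 named comparisons under Bonferroni, the extra loss from using 45 is about 13 points (49% to 36%).

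**Conclusion.** The point holds in limited form. Section 2.6 routes the group-level pre-to-post change through an omnibus test and a Bonferroni family of unstated size, with nothing linking either to the hypotheses. If the family is all pairs of the 10 BDI-II/BAI occasions, pre-post power with 39 completers is about 36% at dz 0.5, against 86% as one planned contrast; at dz 0.8 the loss is about 8 points. These figures rest on an assumed two-sided 0.05, an assumed effect size and the all-pairs reading. They concern the parametric branch.

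Separately, because six of the 10 occasions follow surgery, a significant omnibus result need not reflect any change over treatment.

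A reader might go further and infer a general 50-point loss, blame the gate for it, or conclude that the plan breaks a promise on power. The documents do not support these: the loss shrinks quickly for larger effects or smaller families, the gate adds only a point or two, and no power is stated for this contrast.

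**What to change.** In section 2.6:
- **Hypothesis 1.** Name pre- versus post-treatment as the planned group contrast on each primary score, tested at 0.05 without the omnibus gate and reported with its 95% CI.
- **Hypothesis 2.** Restrict the adjusted family to the comparisons that the article names (post-treatment versus each follow-up, and pre-treatment versus each follow-up), with Holm correction.
- **Both branches.** Use the same contrasts and the same correction whether the parametric or the non-parametric route is taken.
- **Other pairs.** Report follow-up-versus-follow-up differences descriptively.

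The cost is wording only, with the same data and software. There are two downsides. The descriptive pairs carry no formal claim. And detection of relapse remains modest: an isolated 0.5-SD relapse would still be missed in about 41% of cases under Holm over eight contrasts, and in up to about 50% over sixteen. A "maintained" conclusion should therefore rest on the confidence intervals, not on a non-significant test.
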